### Data collection and management

2.6

A baseline evaluation will be carried out to assess the patients' demographics, electrocardiographic data, comorbidities, quality of life, and procedural data related to AFCA. All collected data will be anonymized before being entered into the online database (https://icreat.nih.go.kr). Data collection will occur both at the baseline and after each follow-up evaluation. An independent data monitoring committee will continuously review the study's execution.

### Statistical analyses

2.7

Continuous variables will be expressed as means ± standard deviations or medians with interquartile ranges, depending on the distribution. Categorical variables will be displayed as frequencies and percentages. For comparisons, the Student's t-test or Mann-Whitney *U* test will be employed for continuous variables, while the chi-square test or Fisher's exact test will be utilized for categorical variables, as suitable.

The primary analyses will be performed on the intention-to-treat (ITT) population. For the primary objective, the cumulative event rate during clinical follow-up will be estimated using the Kaplan-Meier method, with a 95 % confidence interval calculated for the difference in event rates. As a sensitivity analysis, the primary endpoint analysis will also be performed on the per-protocol (PP) population. The ITT population will include all randomized patients, compared according to their assigned group regardless of the treatment actually given. The PP population will exclude patients with protocol deviations, including those found to be ineligible, those without informed consent, or those for whom the randomized therapy was not implemented. For secondary endpoints, the incidence or cumulative incidences of each endpoint will be calculated using Kaplan-Meier plots for comparisons. Missing variables will not be imputed for planned analyses, except where specified otherwise. Patients with missing values will be excluded from variable-related analyses but included in analyses not related to the missing variable. Patients lost to follow-up and subsequently lost to assessment of the primary endpoint will be considered censored in the estimation of Kaplan-Meier event rates There is no planned formal interim analysis or guidelines for stopping the study. However, the data and safety monitoring board (DSMB) will review safety data in a blinded manner, with the DSMB statistician providing unblinded summary tables. The DSMB will discuss and determine whether early termination is required due to safety concerns.

Subgroup analyses will be conducted to compare the hazard ratio (HR) of no OAC therapy against OAC therapy, stratified by prespecified subgroups including age (<65 vs. ≥65 years), sex (male vs. female), diabetes (Yes vs. No), hypertension (Yes vs. No), heart failure (Yes vs. No), vascular disease (Yes vs. No), AF type (paroxysmal vs. non-paroxysmal), and time from diagnosis to ablation (<1 year vs. ≥1 year).

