### Sample size estimation

2.5

Based on the assumptions provided, including an annual primary outcome rate of 4.6 % in the OAC therapy group (comprising a 1.0 % annual stroke/systemic embolism rate after AFCA and a 3.6 % annual major bleeding rate observed in a pivotal randomized trial of DOAC) [[27], [28], [29]], the total expected primary outcome rate over 2 years was estimated as 9.2 %. This study aims to show that no OAC therapy will achieve a 5.0 % absolute risk reduction over 2 years (equivalent to a 54 % relative risk reduction driven by the reduction of major bleeding) compared with OAC therapy [29,30]. Considering an anticipated 7 % dropout, and aiming for 80 % power and a 5 % two-sided alpha error, a total of 840 patients will be required, with 420 patients allocated to each arm of the trial.

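### The per-protocol sensitivity analysis repeats an unadjusted Kaplan-Meier difference in a set selected after open-label randomisation; adjusting it for baseline covariates already collected is a cheap, minor improvement.

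*Protocol article*

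**What the plan says.** Section 2.7 (Statistical analyses) of the protocol article makes intention to treat primary. For the primary objective, "the cumulative event rate during clinical follow-up will be estimated using the Kaplan-Meier method", and a 95% confidence interval is given for the difference between arms. No covariate is named. The primary endpoint analysis is then repeated, as a sensitivity analysis, in the per-protocol population: "The PP population will exclude patients with protocol deviations". The deviations listed are ineligibility, absence of consent, and failure to implement the randomised therapy.

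Section 2.6 (Data collection and management) provides for a baseline record of demographics together with "electrocardiographic data, comorbidities, quality of life, and procedural data related to AFCA". In section 2.7, age, sex, diabetes, hypertension, heart failure and vascular disease appear only as subgroup factors. The same section says that missing values are not imputed unless otherwise specified, and that a patient with a missing value leaves the analyses that use that variable.

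**The concern.** Of the three per-protocol exclusions, failure to implement the therapy is decided after allocation, by patients and physicians who know the allocation. Randomisation no longer protects a comparison made after such exclusions. The protocol's own Discussion (section 3) gives a reason to expect the selection to follow risk: an observational study in Japan found more OAC continuation at CHADS2 scores of at least 3 than at 2 or less. If patients who decline to stop OAC are the higher-risk ones, removing them lowers the event rate of the no-OAC arm. That moves the sensitivity result towards the superiority hypothesis it is meant to test. The baseline data needed to reduce this are already collected but have no part in the comparison.

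There is a lesser point of efficiency. The same covariates could sharpen the intention-to-treat difference a little without changing what it estimates.

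**Working it through.** **Inputs (section 2.5, Sample size estimation).** For the OAC arm, "the total expected primary outcome rate over 2 years was estimated as 9.2"%. The target is that "no OAC therapy will achieve a 5.0 % absolute risk reduction over 2 years", so the no-OAC rate is 9.2 − 5.0 = 4.2%. Also "Considering an anticipated 7 % dropout", "aiming for 80 % power and a 5 % two-sided alpha error", and "a total of 840 patients will be required, with 420 patients allocated to each arm of the trial". The documents give neither a non-implementation rate nor the prognostic strength of any covariate, so both are varied below as assumptions.

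**1. The plan's own figure.** With v = 0.092 × 0.908 + 0.042 × 0.958 = 0.123772 and mean rate 0.067:
- Unpooled: n = (1.96 + 0.8416)² × v / 0.05² = 388.6 per arm; divided by 0.93, 417.8.
- Pooled: n = (1.96 × √(2 × 0.067 × 0.933) + 0.8416 × √v)² / 0.05² = 391.3 per arm; divided by 0.93, 420.8.

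The stated 840 is reproduced.

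**2. Events and precision.** Evaluable patients per arm: 420 × 0.93 = 390.6. Expected events: 390.6 × (0.092 + 0.042) = 52.3. Standard error of the difference: √(0.123772 / 390.6) = 1.78 points. Half-width of the 95% interval: 1.96 × 1.78 = 3.49 points.

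**3. Per-protocol selection.** Suppose a fraction f of the no-OAC arm is excluded and its members carry twice the risk r of those who remain. Then 4.2 = (1 − f) r + 2 f r = r (1 + f), so r = 4.2 / (1 + f).
- f = 10%: r = 4.2 / 1.1 = 3.8%; the apparent benefit grows by 0.4 points.
- f = 20%: r = 4.2 / 1.2 = 3.5%; the apparent benefit grows by 0.7 points.

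A simulation with 10 to 13% risk-related non-implementation in the no-OAC arm gave an inflation of about 0.2 to 0.4 points. Adjustment removed it when the covariates driving the selection were the measured ones.

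The direction assumes that selection acts mainly in the no-OAC arm. If the OAC arm lost the same 10% at twice the risk, its rate would be 9.2 / 1.1 = 8.36%. The difference would then be 8.36 − 3.82 = 4.5 points, which is an attenuation.

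**4. Precision gain in the intention-to-treat comparison.** Take a logistic-normal risk score with standard deviation √2 × probit(c), and let q1 and q0 be individual risks by arm. The adjusted variance is [E q1(1 − q1) + E q0(1 − q0)] / n + Var(q1 − q0) / (2n), with n = 391. Unadjusted power (Wald) is 80.2%.

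| Assumed c-statistic | Variance reduction | Power | CI half-width (points) |
|---|---|---|---|
| 0.60 | 0.8% | 80.6% | 3.47 |
| 0.65 | 1.9% | 81.0% | 3.45 |
| 0.70 | 3.7% | 81.7% | 3.42 |
| 0.75 | 6.2% | 82.7% | 3.38 |

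This formula treats the risk score as known. Simulations that fitted a four-covariate logistic working model, with 391 per arm, gave adjusted-to-unadjusted variance ratios of 1.00, 0.99, 0.96 to 0.97 and 0.93 to 0.95 at the same four c-statistics. With eight covariates the ratio was 1.00 at c of about 0.64, so a longer list can use up the gain.

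**The case against.** The strongest reply is that nothing here is an error. The unadjusted intention-to-treat difference is valid under 1:1 randomisation, and its interval already allows for chance imbalance. Even a 5-point imbalance in a factor that doubles risk (an assumption) moves the difference by only 0.05 × 6.7 / (1 + prevalence). That is 0.30 points at 10% prevalence and 0.22 at 50%, against a standard error of 1.78. All of this stands. A reader might infer that the primary result is biased, or that much precision is being lost on strong predictors. The document supports neither. It does not say how well any covariate predicts the composite. In section 2.5, major bleeding supplies 3.6 of the 4.6 points a year, while CHA2DS2-VASc is presented only as a stroke-risk score.

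It can also be said that the per-protocol analysis is only a sensitivity check, that the exclusion rates used above are assumed, and that a supportive adjusted analysis may sit in a statistical analysis plan that is not shown. The first two limit the severity. The third means that the absence of an adjusted intention-to-treat analysis is not in itself a finding. It does not answer the per-protocol point, because section 2.7 fixes that analysis as a repeat of the primary one.

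Finally, adjustment has costs. It needs a working model, and under the stated missing-data rule it could drop randomised patients. It also cannot capture every reason for non-implementation. These objections stand and are reflected in the fix.

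**Conclusion.** The concern holds as a minor point with a cheap remedy. The unadjusted per-protocol comparison is open to selection by risk, and the protocol's Discussion makes that plausible. Under assumed non-implementation of 10 to 20% in the no-OAC arm and doubled risk, the shift is about 0.4 to 0.7 points in favour of no OAC. Under milder, risk-related selection of 10 to 13% it is about 0.2 to 0.4 points. Either is small against a 3.49-point half-width, and neither touches the primary result. A reader might conclude that the per-protocol result is certainly confounded, or that adjustment would make it sound. The documents show only that confounding is plausible, and adjustment deals only with what was measured.

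For the intention-to-treat analysis, covariate standardisation is an option worth about 0 to 6% of variance, or 0 to 2.5 power points, under assumed c-statistics of 0.60 to 0.75. It is not the repair of a defect.

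**What to change.** In section 2.7:
- **Per-protocol analysis.** Estimate the 2-year risk difference with adjustment or inverse-probability weighting for a short, prespecified list of baseline covariates. Candidates are age, heart failure, vascular disease and CHA2DS2-VASc score. Since the score already contains the other three, use either the score or its components, not both in full. State that this removes measured confounding only.
- **Intention-to-treat analysis.** Keep the unadjusted Kaplan-Meier difference as primary. Beside it, report a covariate-standardised 2-year risk difference with the same covariates and a robust or bootstrap 95% interval.
- **Missing covariates.** Specify a rule, as an exception to the no-imputation default, so that no randomised patient is dropped for a missing baseline value.

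The cost is wording and modest programming, with no new data or patients. The downside is a working model on about 52 events, so the list should stay at about four covariates. It should be fixed before outcomes are compared by arm. Because the trial is open-label and has enrolled since July 2020, the date on which the list was fixed should be recorded.

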### Randomization and study procedures

2.3

Eligible patients will be randomized to receive OAC therapy or no OAC therapy in a 1:1 ratio. Randomization will be conducted using a web-response permuted-block method at each participating center. Participants allocated to the OAC therapy group will receive apixaban at a dose of 5 mg twice daily. The apixaban dose will be reduced to 2.5 mg twice daily for patients who meet at least two of the following conditions: 1) age 80 years or older, 2) body weight 60 kg or less, and 3) serum creatinine level above 1.5 mg/dL [21]. In cases where a subject experiences intolerable adverse effects with apixaban, an alternative DOAC may be prescribed. Subjects assigned to the no OAC therapy group will not receive any oral anticoagulant. However, antiplatelet therapy may be administered if clinically indicated (e.g., for percutaneous coronary intervention or acute coronary syndrome) in both groups. All patients underwent ECG at each visit and 24- to 72-h Holter monitoring at least every six months after enrollment. Additionally, Holter monitoring or event recordings were conducted whenever patients reported symptoms of palpitations suggestive of arrhythmia recurrence. If a patient experiences a documented recurrence of atrial arrhythmia or undergoes repeat AFCA during the study period, they will be censored at that point and prescribed anticoagulation based on the patient's stroke risk or periprocedural needs. Subjects will be followed up for a maximal duration of 24 months.

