### Study outcomes

2.4

The primary outcome, assessed at the 2-year mark following randomization, is a composite endpoint comprising stroke, systemic embolism, and major bleeding (see Table 2). Stroke is defined as a sudden, focal neurologic deficit resulting from a presumed cerebrovascular cause that persists for more than 24 h and is not attributable to a readily identifiable cause, such as a tumor or seizure [22]. Systemic embolism is defined as abrupt vascular insufficiency accompanied by clinical or radiological evidence of arterial occlusion, occurring in the absence of other likely mechanisms (e.g., trauma, atherosclerosis, or instrumentation). Major bleeding events will be defined according to established criteria [22]. Major bleeding was defined by the International Society on Thrombosis and Hemostasis (ISTH) criteria [23].

**Table 2 tbl2:** Study outcomes.

Primary outcome
A composite of stroke, systemic embolism, and major bleeding (defined by the ISTH criteria)

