**Secondary outcome**
Stroke
Systemic embolism
ISTH major bleeding
ISTH clinically relevant non-major bleeding
All-cause death
Myocardial infarction
Pulmonary thromboembolism
Hospitalization
AFQET
K-MoCA
Frailty (Questionnaire and grip strength)

AFQET, Atrial Fibrillation Effect on QualiTy-of-Life; ISTH, International Society on Thrombosis and Hemostasis; K-MoCA, Korean version of Montreal Cognitive Assessment.

Secondary outcomes of the study will include the individual components of the primary outcome, namely stroke, systemic embolism, and major bleeding events. Additionally, we will evaluate the incidence of clinically relevant nonmajor bleeding, as defined by the ISTH criteria [24]. Additional secondary outcomes encompass all-cause mortality, myocardial infarction (MI), pulmonary thromboembolism (PTE), transient ischemic attack (TIA), and hospitalization due to any cause. The definitions of MI and PTE are presented in Supplement. TIA will be defined as the presence of a new focal neurologic deficit presumed to be vascular in origin, with signs or symptoms lasting less than 24 h, without evidence of infarction as assessed by brain imaging [25]. The Atrial Fibrillation Effect on QualiTy-of-life (AFEQT) [26], frailty assessments (including questionnaires and grip strength measurement), and the Korean-Montreal Cognitive Assessment will be evaluated at baseline, as well as at the 1-year and 2-year follow-up time points. Adjudication of study outcomes will be performed by an independent clinical event adjudication committee, which will remain blinded to the primary results of the study.

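### Kaplan-Meier is used for event endpoints that exclude other-cause death, so absolute 2-year risks, and with them the risk difference, will be slightly off

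*Protocol article*

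**What the plan says.** The primary outcome in section 2.4 is "a composite endpoint comprising stroke, systemic embolism, and major bleeding", assessed 2 years after randomization. All-cause death is not a component. It appears only as a separate secondary outcome, next to other events: "Additional secondary outcomes encompass all-cause mortality, myocardial infarction (MI), pulmonary thromboembolism (PTE), transient ischemic attack (TIA), and hospitalization due to any cause". The individual components of the composite and clinically relevant non-major bleeding are also secondary outcomes.

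Section 2.7 names one estimator for all of these. For the primary objective, "the cumulative event rate during clinical follow-up will be estimated using the Kaplan-Meier method", with a 95% confidence interval for the difference in rates. For secondary endpoints, "the incidence or cumulative incidences of each endpoint will be calculated using Kaplan-Meier plots for comparisons".

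The article states two censoring rules. In section 2.7, patients lost to follow-up and to assessment of the primary endpoint "will be considered censored in the estimation of Kaplan-Meier event rates". In section 2.3, after a recurrence of atrial arrhythmia or a repeat ablation, "they will be censored at that point and prescribed anticoagulation based on the patient's stroke risk or periprocedural needs". Neither rule mentions death, and no competing-risk method is named.

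**The concern.** A patient who dies of a cause outside the endpoint can no longer have a stroke, an embolism or a bleed. Kaplan-Meier has no category for this. Such a death is not an event, so it can only be a censoring time, and the patient is then treated as still able to have the event later. One minus Kaplan-Meier estimates the risk that would be seen if nobody died of anything else, and that exceeds the proportion of patients who actually have the event by 2 years.

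The primary result is an absolute difference between two such risks, and the article's Discussion frames the trial as a question of net clinical benefit. Both call for the probability of an event among patients who can also die. Any excess in an arm's rate passes directly into the reported difference.

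**Working it through.** **Inputs.** From section 2.5: 2-year primary risk of 9.2% on anticoagulation (2 × 4.6% per year), an absolute reduction of 5.0 points and hence 9.2% − 5.0% = 4.2% without anticoagulation, 80% power, 5% two-sided alpha, 7% dropout, 420 per arm. The article gives no mortality figure. Two-year death without a prior event, m, is therefore an assumption, varied from 1% to 5%.

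**The plan's own figure.** The pooled two-proportion formula for 9.2% against 4.2% gives 392 per arm. Allowing for 7% dropout gives 392 / 0.93 = 422 or 392 × 1.07 = 420. The stated 420 is reproduced, so 9.2% and 4.2% are the planning risks.

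**Formula.** Assume constant hazards over 2 years. Let F be the risk that Kaplan-Meier estimates. The cumulative event hazard is l = −ln(1 − F) and the cumulative hazard of other death is d = −ln(1 − m). The cumulative incidence with death competing (Aalen-Johansen) is

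l / (l + d) × (1 − exp(−(l + d))).

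**One case in full, m = 5% in both arms.** d = −ln(0.95) = 0.0513.

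- On anticoagulation: l = −ln(0.908) = 0.0965. The share is 0.0965 / 0.1478 = 0.653, and 1 − exp(−0.1478) = 0.1374. The risk is 0.653 × 0.1374 = 8.97%, against 9.20% by Kaplan-Meier.
- Off anticoagulation: l = −ln(0.958) = 0.0429. The share is 0.0429 / 0.0942 = 0.4555, and 1 − exp(−0.0942) = 0.0899. The risk is 0.4555 × 0.0899 = 4.09%, against 4.20%.
- Difference: 4.88 points, against 5.00.

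**Range.**

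| Assumed 2-year death, on / off anticoagulation | Risk on | Risk off | Difference (points) |
|---|---|---|---|
| none (Kaplan-Meier figure) | 9.20% | 4.20% | 5.00 |
| 1% / 1% | 9.15% | 4.18% | 4.98 |
| 3% / 3% | 9.06% | 4.14% | 4.93 |
| 5% / 5% | 8.97% | 4.09% | 4.88 |
| 5% / 2% | 8.97% | 4.16% | 4.81 |
| 2% / 5% | 9.11% | 4.09% | 5.01 |

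**What drives the excess.** It grows with the event rate as well as the death rate. With 3% deaths on anticoagulation and 5% off, Kaplan-Meier overstates the first arm by 9.20 − 9.06 = 0.14 points and the second by 4.20 − 4.09 = 0.11 points, so the arm with fewer deaths has the larger excess.

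**Scale for comparison.** The standard error of the difference is √[(0.092 × 0.908 + 0.042 × 0.958) / n]. This is 1.78 points at n = 390 (420 less 7% dropout) and 1.72 at n = 420, which gives 95% half-widths of 1.96 × 1.78 = 3.5 and 1.96 × 1.72 = 3.4 points. The largest shift in the table, 5.00 − 4.81 = 0.19 points, is about 5% of that.

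**The case against.** The strongest objection is that this is immaterial and conventional. Kaplan-Meier for a composite without all-cause death over 24 months is common practice. The eligibility criteria exclude active malignancy, life expectancy under 1 year, significant renal or liver disease and significant structural heart disease, so few deaths are likely, and the 5% scenario has no support in the article. The shift is a small fraction of the confidence interval. All of this stands, and it sets the priority of the point.

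It can also be said that competing-risk detail belongs in an analysis plan that is not shown. That would answer a complaint about silence. Here, however, the article names the estimator, and for endpoints that exclude other-cause death that estimator does not give the cumulative incidence.

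Several stronger readings are tempting but not supported:

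- A reader might infer that the plan orders deaths to be censored. It does not mention them; censoring follows from the choice of estimator.
- A reader might infer that the primary result is mislabelled as a cumulative incidence. Section 2.7 calls it a cumulative event rate and uses incidence wording only for secondary endpoints.
- A reader might infer that the excess is always larger in the arm with more deaths, or that it cancels when mortality is equal. The 3%/5% case contradicts the first and the equal-mortality rows contradict the second.
- A reader might extend the point to every outcome. A stroke, embolism or major bleed that proves fatal is itself an event and is not affected. AFEQT, K-MoCA and frailty are scale measures. The subgroup analyses compare hazard ratios, not absolute risks, so this bias does not apply to them.

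**Conclusion.** The point holds as a low-priority improvement to the absolute-risk estimates. As written, section 2.7 will slightly overstate each arm's 2-year risk for the primary composite and for every time-to-event secondary outcome other than all-cause death, provided some patients die without an event. At the planning risks, and with an assumed 1% to 5% two-year death without a prior event, the primary difference moves from 5.00 to between 4.98 and 4.88 points at equal mortality. It moves to 4.81 or 5.01 in the two unequal cases shown.

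These figures rest on constant hazards and on mortality that the article does not give. A reader might infer that the trial's conclusion is at risk. The size does not support that: the shift is far inside the confidence interval.

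**What to change.** In section 2.7, estimate each arm's 2-year risk by the Aalen-Johansen cumulative incidence function, with death that is not part of the endpoint as a competing event, and take the 95% confidence interval for the difference from it. Do this for the primary composite and for each time-to-event secondary outcome other than all-cause death. Keep Kaplan-Meier for all-cause death, and report deaths by arm beside the composite.

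The cost is a change of wording. All-cause death is already a study outcome, so no new data item is needed, and alpha, sample size and patient burden are unaffected. Fixing the method in advance also avoids a post hoc choice if mortality turns out to differ between arms.

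This change does not deal with censoring at arrhythmia recurrence or repeat ablation in section 2.3. That is a separate issue and probably a larger one, and while that rule stands the Aalen-Johansen estimate will still not be a fully real-world 2-year risk.
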